**11.4.3 Assessment by the Clinical Research Leader and the Trial Secretariat Office**

In the event that the Clinical Research Leader receives case reports on adverse reactions, he is to assess their urgency, importance or implications, and to give instructions the Data Center and the participating healthcare institutions of interest, as to their handling, including putting these cases on hold, as required. The Clinical Research Leader may communicate these instructions by telephone depending on the urgency of the cases, followed by those in writing (i.e., by facsimile, mail or e-mail).

The Clinical Research Leader is to communicate his interpretation of the adverse reactions reported as well as their handling (including judgment as to continuation or termination of the study) to the Principal Investigator within 72 hours of their knowledge of occurrence of the adverse reactions, to ask for judgment regarding the validity of their judgment and handling of the cases and forward the "Case Report on Adverse Reactions" sent to them by the reporting healthcare

institutions. Assessment of serious adverse reactions by the Clinical Research Leader should include an evaluation of the each subject's clinical course, as well as of whether or not the frequency of each reported adverse reaction is within their anticipated range. If the Clinical Research Leader judged their frequency to be beyond their anticipated range, the Clinical Research Leader is to document such judgment for reporting.

The Principal Investigator is to submit all reported adverse reactions to the Safety Assessment Committee for review. The Safety Assessment Committee is to review all reported adverse reactions, and to make recommendations to the Principal Investigator with regard to the handling of the cases (including judgment as to whether the study is to be continued with the subjects, instructions are required to the healthcare institutions of interest, or the trial protocol calls for revision). The Principal Investigator is then to give instructions to the Clinical Research Leader in accordance with these recommendations.

### **11.5 Analysis of adverse reactions through regular monitoring**

The Clinical Research Leader and the Trial Secretariat Office are to analyze monitoring reports produced by the Data Center through regular monitoring, and to develop reports on the results of their analysis, where all adverse reactions not reported as urgent are to be evaluated with regard to their category, severity, and rate of occurrence, to determine if they require reporting to the healthcare institutions of interest or call for revision of the trial protocol. At the same time, the Clinical Research Leader and the Data Center are to ensure: that no adverse reactions are left out/missed in the reports submitted by the healthcare institutions; that all reported adverse reactions are entered in regular monitoring reports; and that the results of their analysis include their judgment as to whether there were any adverse reactions left out/missed in the reports received from the participating healthcare institutions.

### **11.6 Adverse reactions to be anticipated**

All investigators are to refer to the package inserts and the product monographs of the drugs to be used in the trial for information on anticipated adverse reactions with the drugs as well as their rate of occurrence.

Specifically, anticipated adverse reactions include hypoglycemia, edema, cardiac failure, gastrointestinal symptoms including nausea/vomiting and discomfort, anemia, palpitation, skin rash, eczema, high CPK values, rhabdomyolysis, lactic acidosis, leucopenia, thrombocytopenia, hyperkalemia, and abnormal GOT/GPT values.

## **12. Statistical analysis**

### **12.1 Objective**

The objective of the statistical analysis is to verify the superiority of intensive therapy over conventional therapy as reference/control. With the primary endpoint defined as the "occurrence of either of myocardial infarction, coronary bypass surgery, percutaneous transluminal coronary angioplasty, stroke, carotid endarterectomy, percutaneous transluminal cerebral angioplasty, carotid artery stenting, or death", the study is designed to verify that intensive therapy is associated with significantly longer event-free survival (time to occurrence of either of myocardial infarction, coronary bypass surgery, percutaneous transluminal coronary angioplasty, stroke, carotid endarterectomy, percutaneous transluminal cerebral angioplasty, carotid artery stenting, or death). In other words, the null hypothesis (H0) of the current trial and its alternative hypothesis (H1) are defined as follows, where when we reject H0 in favor of H1, we conclude that intensive therapy is a useful therapeutic modality.

H0: When the occurrence of either of myocardial infarction, coronary bypass surgery, percutaneous transluminal coronary angioplasty, stroke, carotid endarterectomy, percutaneous transluminal cerebral angioplasty, carotid artery stenting, or death is defined as an event, intensive therapy and conventional therapy are comparable in event-free survival.

H1: When the occurrence of either of myocardial infarction, coronary bypass surgery, percutaneous transluminal coronary angioplasty, stroke, carotid endarterectomy, percutaneous transluminal cerebral angioplasty, carotid artery stenting, or death is defined as an event, intensive therapy is associated with longer event-free survival than conventional therapy.

The secondary endpoints of the study are defined as the following four events.

1. Occurrence of either of myocardial infarction, stroke, or death
2. Onset or progression of nephropathy
3. Occurrence of lower limb vascular events (amputation or revascularization of lower limb)
4. Onset or progression of retinopathy

Of these, onset or progression of nephropathy is also considered an important event; therefore, the current trial is to verify the superiority of intensive therapy over conventional therapy with regard to this event-free survival. In the event that intensive therapy has been proven to be superior to conventional therapy in secondary endpoint 1, we conclude that intensive therapy is a useful therapeutic modality. As the primary and secondary endpoints are not independent of one another, the statistical inference is to be adjusted for multiplicity by using the re-sampling method.

Of note, secondary endpoint 2 was included to complement the primary endpoints. Therefore, only exploratory analysis is to be performed on this endpoint and not to be used as a rationale for the main conclusions to be drawn. In other words, whether or not intensive therapy is superior to conventional therapy in reducing macrovascular complications is to be determined on the basis of an analysis of the primary endpoints.

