### **12.3.3 Other analyses**

To complement analyses of the primary endpoints, three kinds of analyses (descriptive statistics, hypothesis testing and effect size estimates) are to be performed on the secondary endpoints. However, being exploratory in nature, these analyses are not to be adjusted for multiplicity.

Fisher's direct exact probability estimation is to be used to compare the percentages of occurrence of adverse reactions between the two treatment arms as part of the safety evaluation, and 95% confidence intervals (CI) for the differences detected. Accurate confidence intervals are to be estimated based on the bimodal distribution of the data.

Otherwise, exploratory analyses are to be performed as required. When such analyses are to be performed, their details

are to be described in the Statistical Analysis Plan.

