## **12.4 Interim Analyses and the Clinical Trial Review Committee**

### **12.4.1 Interim analyses**

To assess whether the main objectives of the study have been achieved, 3 interim analyses were planned as follows. These analyses were to be performed by independent statistical analysts at the Data Center.

- Early after completion of the subject study registration
- 1 year after completion of the subject study registration
- 2 years after completion of the subject study registration

However, as the general survey conducted in June 2006 demonstrates that fewer subjects had been accrued to date and fewer events were reported than initially expected, interim analyses are to be performed based the nine general surveys scheduled to place at the following time points:

- December 2007
- December 2008
- December 2009
- December 2010
- June 2011
- June 2012
- June 2013
- June 2014
- June 2015

Data reviewed by the Endpoint Assessment Committee are to be used for analysis at each of the interim analyses. Unless otherwise notified, the study subjects are to continue their study registration even during the interim analyses. Once the interim analysis results have demonstrated that the main objectives of the study have been achieved, the trial is to be discontinued and the study results to be released.

To reduce the Type 1 error associated with the multiple analyses (interim and final analyses) and to maintain the two-sided Type 1 error at 5%, analyses of the primary endpoints are to be adjusted for multiplicity by using a Lan-DeMets alpha function approach with an alpha -spending function of the O'Brien-Fleming type. In addition, Bayesian Probability or conditional power is to be calculated as reference data.

Of the secondary endpoints, "time to onset or progression of nephropathy or occurrence of death" is to be analyzed with adjustment by the re-sampling method for multiplicity in relation to the primary endpoints. No inter-group comparisons are to be made except this endpoint, unless the Trial Assessment Committee or the Central Ethics Committee approves such comparison.

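### Section 12.1 contradicts itself on which secondary endpoint can support a conclusion: nephropathy is confirmatory by name but exploratory by number

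*Protocol*

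**What the plan says.** The list in section 12.1 reads "1. Occurrence of either of myocardial infarction, stroke, or death" and "2. Onset or progression of nephropathy", followed by lower limb vascular events and retinopathy. Sections 1.7 and 10.2 use the same order.

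The text after the list in 12.1 assigns roles. By name: "Of these, onset or progression of nephropathy is also considered an important event", and so "the current trial is to verify the superiority of intensive therapy over conventional therapy with regard to this event-free survival". It then turns to numbers. Superiority on secondary endpoint 1 is enough to conclude that intensive therapy is useful, with multiplicity handled by re-sampling. Of the other it says: "Of note, secondary endpoint 2 was included to complement the primary endpoints. Therefore, only exploratory analysis is to be performed on this endpoint", and adds that this endpoint may not serve as a basis for the main conclusions. The closing sentence restates this as meaning that macrovascular benefit is judged on the primary analysis.

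Section 12.4.1 says that time to nephropathy or death "is to be analyzed with adjustment by the re-sampling method for multiplicity in relation to the primary endpoints", and allows no between-group comparison of the other secondary endpoints at interim without committee approval.

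Section 12.3.2 attaches the adjusted inference and the usefulness conclusion to the secondary analyses without naming an endpoint. Section 12.3.3 plans further analyses of the secondary endpoints, again unnamed: "However, being exploratory in nature, these analyses are not to be adjusted for multiplicity".

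**The concern.** The protocol lets a secondary endpoint support a conclusion about the therapy, so the identity of that endpoint is a decision rule. As written, the rule gives nephropathy two roles that exclude each other: superiority is to be verified on it, yet it may receive only exploratory analysis.

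If the numbers are followed, a positive nephropathy result could not support a main conclusion. MI, stroke or death, which repeats part of the primary composite and adds little independent evidence, could support the usefulness claim. If the names are followed, the roles reverse. An SAP that adopted either reading would still conflict with one sentence of the protocol.

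**Working it through.** No figure in the protocol is at stake, so the check sets the statements side by side.

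**Step 1: the numbering.** Sections 1.7, 10.2 and 12.1 agree: 1 is MI, stroke or death; 2 is nephropathy. The order is the same in three places, so it is not a slip in one list.

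**Step 2: the role each statement gives, under that numbering.**

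| Statement | Nephropathy | MI, stroke or death |
|---|---|---|
| 12.1, by name | superiority to be verified | not mentioned |
| 12.1, "secondary endpoint 1" rule | none | supports usefulness |
| 12.1, "secondary endpoint 2" rule | exploratory only | none |
| 12.4.1, by name | only secondary adjusted with the primary (as nephropathy or death) | no interim comparison without approval |

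Rows 1 and 3 of the nephropathy column cannot both hold. Row 3 also conflicts with row 4.

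**Step 3: exchange the two labels in 12.1 and read again.** Four features then fit:

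1. The usefulness sentence directly follows the sentence that names nephropathy, and becomes its natural continuation.
2. The exploratory endpoint is described as complementing the primary. MI, stroke and death are all components of the primary composite (section 10.1); a renal outcome is not.
3. The exploratory status is explained through macrovascular complications. Section 4 classes nephropathy as microvascular.
4. Section 12.4.1 singles out nephropathy (with death) for adjustment jointly with the primary. Section 4 also gives a specific reason for studying nephropathy.

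With the labels exchanged, 12.1 agrees with itself and with 12.4.1. Apart from the numbers themselves, nothing in 12.1 or 12.4.1 points the other way.

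**Step 4: do 12.3.2 and 12.3.3 settle it?** No. Neither names the endpoint it covers. Read literally, each secondary endpoint falls under both the adjusted and the unadjusted rule.

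**Step 5: the endpoint's definition.** The lists in 10.2 and 12.1 give nephropathy alone. Section 12.3.2 counts death as an event in every secondary event-free survival, and 12.4.1 writes nephropathy or death. The correction should use one form.

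**The case against.** The strongest reply is that intent can be recovered. Nephropathy is identified by name in both 12.1 and 12.4.1, and the closing sentence of 12.1 reserves any macrovascular conclusion for the primary endpoint under either reading. Sections 12.3.2 and 12.3.3 also carry different titles, and 12.3.3 speaks of complementing the primary, so a coherent reading is that the first covers the confirmatory secondary and the second the rest. Most of this stands. It makes the 12.3.2/12.3.3 problem one of loose scope wording rather than a separate contradiction, and it limits the room for choosing an endpoint after the results. It does not remove the sentence that makes nephropathy exploratory.

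Two stronger readings are tempting and are not supported.

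- A reader might infer an inflated false-positive rate: for two independent tests at an unadjusted 5%, 1 − 0.95² = 9.75% (about 8.3% at an assumed correlation of 0.7 and 7.0% at 0.9), and for five, 1 − 0.95⁵ = 22.6%. These figures assume no adjustment. The protocol prescribes re-sampling for the secondary that can support a claim (12.1, 12.3.2, 12.4.1), and 12.3.3 gives its unadjusted exploratory analyses no power to support one. It states no correlation either. The figures are illustrations at most.
- A reader might take the swap as established. It is a well-supported inference; the protocol nowhere states which reading was meant.

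**Conclusion.** The contradiction is real and lies in the current text: under the protocol's own numbering, nephropathy is both an endpoint on which superiority is to be verified and one that cannot support a main conclusion. The most likely cause is that the two labels were exchanged in 12.1. That conclusion rests on the order of the sentences, the complementary and macrovascular wording, and the interim plan, and needs the sponsor's confirmation.

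The effect is confined to the secondary claim, where it decides which endpoint may support a conclusion. The primary hypothesis, its test and its two-sided 5% level are untouched, and no error rate can be put on the ambiguity from the documents. It still needs correction before unblinded analysis, because a stated decision rule is wrong as written.

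**What to change.** In 12.1, replace the endpoint numbers with names. Subject to the sponsor's confirmation:

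- nephropathy, or death as in 12.3.2 and 12.4.1, is the single confirmatory secondary endpoint under the re-sampling adjustment;
- MI, stroke or death is complementary and exploratory.

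In 12.3.2, state that the adjusted inference and the usefulness conclusion apply to that one endpoint. In 12.3.3, state that the unadjusted exploratory analyses cover the other three: MI, stroke or death; lower limb events; retinopathy. Use the same form of the nephropathy endpoint wherever its confirmatory role is stated.

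The cost is wording in three subsections, with no change to data collection or sample size. Timing needs care. Section 13 reports that enrolment has ended at 2,542 patients, 12.4.1 schedules interim analyses from December 2007 to June 2015, and 12.4.2 counts the Clinical Research Leader as part of the committee that sees their results. The sponsor should therefore confirm the intent from design records, through people without access to unblinded results, and document this with the amendment.

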### **12.2 Subjects of analysis**

The hypotheses for the event-free survivals described above are to be tested in "all subjects judged to be eligible for

inclusion in the study". The decision as to whether or not any particular subject is eligible is to be left up to the designated Clinical Research Leader, the Trial Secretariat Office and the trial statisticians. Additionally, the above hypotheses are also to be tested in "all subjects registered with the study" to confirm the certainty of the conclusions to be drawn.

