## 6. Study design

### 6.1 Processes

The present trial is a multi-center, open-label, randomized parallel-group study conducted to compare the efficacy of intensive versus conventional therapy in type 2 diabetic patients with HbA1c 6.9% or greater. The overall procedure from patient informed consent to completion of patient data evaluation is as described below.

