#### (2) Interim study registration

After obtaining informed consent, the physician in charge is to perform examinations on items set forth in section 9.1 in each subject. However, available chest x ray, electrocardiogram (ECG) and fundoscopic data for the subject that is up to 6 months old may alternatively be used. The physician in charge is to forward his judgment as to the eligibility of the subject to the central Data Center for the subject to be enrolled in the study on an interim basis.

Based on the information forwarded by the physician in charge, the Data Center is to verify the eligibility of the subject thus registered, and to inform the physician in charge of the subject's interim registration when the subject was found eligible. The Data Center is also to inform the physician in charge of its judgment when the subject was found otherwise (ineligible).

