#### 8.6 Random assignment

The study subjects are to be assigned to the investigational treatment in which the responsibility for such assignment is to rest solely with the trial statistician, and the allocation code used is not to be disclosed to any of the healthcare institutions or physicians participating in the study. In random assignment, dynamic allocation is used with the presence or absence of cardiovascular disease (myocardial infarction, stroke, coronary bypass surgery, percutaneous coronary angioplasty, cerebral revascularization\*1, or cerebrovascular reconstruction\*2), male/female ratio, age ( $\geq 60$ , < 60 years old) and HbA1c ( $\geq 8.9\%$ , < 8.9%) serving as adjustment factors to ensure a balanced allocation of the subjects between the treatment arms, and the trial statistician is to record the algorithm used in allocation in a separate document.

Note: Cerebral revascularization\*1: Carotid endarterectomy, percutaneous angioplasty, and stent placement  
Cerebrovascular reconstruction\*2: Thrombolysis

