### **12.4.2 Reporting on/review of statistical analyses**

The independent statistical analysts are to draft and submit the interim analysis reports to the Trial Assessment Committee, which is in turn to make its decision as to the continuation of the study, and to make its recommendations to the Principal Investigator, the Foundation Secretariat, and the Clinical Research Leader.

Unless the Trial Assessment recommends discontinuing the study, no personnel except for the Trial Assessment Committee is to be given access to the results of the interim analyses. The Trial Assessment Committee is obliged not to disclose the interim analysis data to any personnel outside the Trial Assessment Committee. However, the Clinical Research Leader is to be construed as forming part of the Trial Assessment Committee.

The Clinical Research Leader is to make the decision as to whether the trial is to be continued or discontinued or the trial protocol is to be revised in part, on the recommendation of the Trial Assessment Committee. In the event that the trial is to be discontinued or the trial protocol is to be revised in part, the Clinical Research Leader is to submit a "request for early termination of the trial" or "request for the revision of the trial protocol" in writing. The Operations Committee is to review the request, and to obtain the approval of the Central Ethics Committee if the Trial Administrative Committee is to decide to revise the trial protocol in part. Upon approval by the Central Ethics Committee, the Clinical Research Leader is to be entitled to revise the trial protocol as requested.

The Clinical Research Leader is to be entitled to raise an objection to the recommendations of the Trial Assessment Committee. The Trial Assessment Committee is to be entitled to make its recommendations again after deliberations. In the event of failure to harmonize the views between the Clinical Research Leader and the Trial Assessment Committee, The Trial Administrative Committee is to make a final decision as to the continuance or discontinuance of the trial or revision of the trial protocol.

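### Section 12.2 runs the confirmatory tests on a judged-eligible subset of the randomised subjects, picked by trial leaders in an open-label trial, instead of on everyone randomised

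*Protocol*

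**What the plan says.** Section 12.2 of the protocol names two analysis sets and ranks them. "The hypotheses for the event-free survivals described above are to be tested in" the subjects judged eligible for inclusion. On who judges, it says: "The decision as to whether or not any particular subject is eligible is to be left up to the designated Clinical Research Leader", along with the Trial Secretariat Office and the trial statisticians. The same hypotheses are then tested in all registered subjects, with the stated purpose "to confirm the certainty of the conclusions to be drawn". The section does not say what follows if the two analyses disagree.

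Other sections bear on how this works in practice:

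- Section 6.1 describes a "multi-center, open-label, randomized parallel-group study".
- Under interim study registration in 6.1, "the Data Center is to verify the eligibility of the subject thus registered". Under final study registration the Data Center may still reject a subject, and assignment takes place at that step.
- Section 11.4.3 has the Clinical Research Leader receive and assess adverse reaction case reports. Under 11.4.1, serious reactions include fatal ones, and death is part of the primary endpoint.
- Section 12.4.2 restricts interim results to the Trial Assessment Committee and adds that "the Clinical Research Leader is to be construed as forming part of the Trial Assessment Committee".
- Section 8.6 says of allocation that "the responsibility for such assignment is to rest solely with the trial statistician".

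**The concern.** Randomisation protects the comparison only while the analysed groups are the groups that were randomised. If subjects can be taken out afterwards by people who may know the arm, or whether an event occurred, the comparison no longer rests on randomisation alone. Section 12.2 gives the leading role to the reduced set.

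No bad intent is needed. Some exclusion criteria in 7.2 are judgements: type 1 diabetes strongly suspected, suspected secondary hypertension, ineligibility in the physician's opinion. Section 7.3 recognises that type 1 diabetes may come to light during treatment. Section 8.2.1 sets at least monthly visits in the intensive arm until March 2010, and 8.2.2 states no such schedule for conventional therapy. Late discoveries of ineligibility could therefore be more frequent in one arm.

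At stake is the primary superiority claim, and with it any secondary claim tested in the same set.

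**Working it through.** **Step 1. Can the two sets differ without removing randomised subjects?** Section 6.1 puts the Data Center's eligibility checks before assignment, and assignment is part of final registration. Registered subjects are therefore randomised subjects. A judged-eligible set smaller than the registered set can arise only by taking randomised subjects out. Section 12.2 does not state the timing; this follows from 6.1 and from the contrast between the two sets.

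**Step 2. What set do the design figures use?** Inputs from section 13: 2,542 enrolled (1,271 per arm, section 6.2), annual event rates 2.2% and 1.5347%, accrual 2.5 years, follow-up 4.25 years, 250 events, two-sided 5%, power at least 80%.

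- Hazard ratio: 1.5347/2.2 = 0.698, about 0.70.
- Power (Schoenfeld): Φ(√250/2 × |ln 0.70| − 1.960) = Φ(2.820 − 1.960) = 80.5%; with 0.698 it is 81.2%.
- Expected events per arm: n × [1 − (e^(−λF) − e^(−λ(A+F)))/(λA)], with λ = −ln(1 − rate), n = 1,271, A = 2.5, F = 4.25. This gives 146.2 + 103.6 = 249.8.

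The plan's 250 events and 80% power are reproduced, and they rest on everyone enrolled. Making all randomised subjects the primary set alters neither.

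**Step 3. How sensitive is the test to selective removal?** This is an illustration only: the documents give no number of exclusions, the starting split is assumed, and every removal is assumed to be an intensive-arm subject with an event. With equal exposure, z ≈ (C − I)/√(C + I), where C and I are conventional and intensive events.

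| Removed | C v I | z | nominal p |
|---|---|---|---|
| 0 | 139 v 111 | 28/√250 = 1.77 | 0.077 |
| 1 | 139 v 110 | 29/√249 = 1.84 | 0.066 |
| 3 | 139 v 108 | 31/√247 = 1.97 | 0.049 |
| 4 | 139 v 107 | 32/√246 = 2.04 | 0.041 |
| 5 | 139 v 106 | 33/√245 = 2.11 | 0.035 |

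Each removal moves z by about 0.07.

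**Step 4. Which boundary applies?** Section 12.4.1 schedules nine interim analyses with O'Brien-Fleming-type spending. If all nine spend alpha (0.025 on each side), the final critical value for ten looks is about 2.08 to 2.09, depending on the assumed information times; some timings give values down to about 2.05. Three removals (1.97) and four (2.04) fall short of that whole range, and five (2.11) pass it. Five subjects are 5/1,271 = 0.4% of the arm and 5/250 = 2% of the events.

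**The case against.** The strongest case against has four parts.

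**The full-set test is mandatory.** A reader might infer that the randomised set could never overturn the result. The protocol does not say so. It requires the same hypotheses to be tested in all registered subjects, so an exclusion that changed the answer would be visible. This stands. What remains is that the text gives the full-set test a confirming role and is silent on disagreement.

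**Access to outcomes by arm is limited.** A reader might infer that all three deciding parties see results by arm. That is not shown. Section 8.6 gives the trial statistician the allocation, but interim analyses are run by separate independent analysts, and no section gives the trial statisticians or the Secretariat outcomes by arm before the final analysis. Even the Leader's position is not uniform: 12.4.2 counts the Leader within the committee yet has the committee make recommendations to the Leader, and 19.5 lists the Leader as attending in addition to the members. The firmer grounds are the open-label design and the case reports under 11.4.3. No section says that any decider would use such knowledge.

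**Timing and masking may be in the statistical analysis plan.** That is fair, and their absence from 12.2 is not counted here. Many entry criteria are also numeric baseline facts, which limits discretion, and exclusions on baseline facts applied alike in both arms need not bias the comparison. But the protocol itself fixes which set leads and who decides membership, and masked adjudication would not change that ranking.

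**The example is a constructed worst case.** It is. The tempting version, that three removals turn p 0.077 into p 0.049, fails under the planned sequential design. It would hold only against a critical value of 1.96, that is, if no alpha was spent at interim. Section 13 says that no interim analysis aimed at stopping for superiority has been conducted, but does not say what this does to the spending in 12.4.1.

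**Conclusion.** The point holds as a poor stated choice of primary analysis set. Section 12.2 gives the confirmatory role to a set that can differ from the randomised population only by removals, leaves those removals to trial leaders in an open-label trial, and does not say which analysis governs if the two disagree.

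The size of any bias cannot be derived from the documents. On the stated assumptions (139 v 111 starting split, equal exposure, all removals being intensive-arm events, all nine looks spending alpha), about five removals would turn a non-significant primary result into a significant one. Exclusions unrelated to arm and outcome would cost only a little power.

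The conclusion does not depend on anyone misusing information, nor on the full-set result being suppressed, which the plan does not allow for. The 250-event, 80% power statement is correct and unaffected.

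**What to change.** Rewrite section 12.2 so that:

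- the primary analysis and the confirmatory secondary analyses include every subject who completed final registration and was assigned, analysed in the assigned arm;
- this analysis governs the conclusion;
- the eligible set becomes a sensitivity analysis, with exclusions resting only on pre-randomisation data and decided masked to arm and outcome.

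The cost is about two sentences in 12.2, with no new data and no change to events or power. The downside is that a few ineligible subjects stay in the primary analysis and may dilute the estimate slightly; the sensitivity analysis will show by how much.
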